### Power considerations

Participating schools invite students who meet the inclusion criteria (i.e. reported sick four times in 12 weeks or more than six consecutive school days) to participate in the study. We will include 480 students, 240 in the control group and 240 in the intervention group. Allowing a loss-to-follow-up of 50% we assume to have complete data on 240 students (120 in the intervention and 120 in the control group). Taking into account cluster randomization with Intra Class Correlation of 0.10, assuming 15 participants per school class and an equal standard deviation (SD) of medical absenteeism in hours during a period of 12 weeks before T1 of 30 h [42], alpha 0.05 and a power of 0.80, in the case of one-sided testing, a difference in medical absenteeism of 15 h between Intervention and Control group at T1 can be established.

### Statistical analyses

In order to evaluate effect of the effect of the intervention the scores on outcomes of both groups measured during follow will be compared, adjusted for baseline findings. For continuous outcome measures such as duration of the medical absenteeism and psychometric test results (multiple) linear regression analyses will be applied. Dichotomous outcomes, such as progressing into the next year or obtaining a basic educational qualification degree, will be evaluated by using a multiple logistic regression analysis.

The research condition will be included as an independent variable. Baseline values of the outcomes are added to the model as covariates. As students are clustered within school locations multilevel analyses will be applied.

Potential moderation of intervention effects by gender, family situation, ethnicity, psychosocial and psychiatric problems (depression, drug abuse, ADHD) is explored by adding an interaction term to the regression models. Stratified analyses will be performed when significant interactions (*p* < 0.10) are observed.

Experiences of students and YHC professionals with the different elements of the MASS intervention as performed by YHC professionals will be evaluated by performing descriptive analyses.

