### Participants

#### Youth health care organizations, schools and youth health care professionals

This study will be conducted in the Dutch regions of Amsterdam, Utrecht, West Brabant and Rotterdam. School recruitment will be organized in collaboration with three YHC organizations associated to the regions of Amsterdam, Utrecht and West Brabant. The YHC organization in Rotterdam will not be involved in the study as schools in this area have not yet implemented the MASS intervention and will therefore be allocated to the control group.

YHC organizations invite the intermediate vocational education schools to participate in the study. Schools that agree to participate will subsequently be visited by the researchers. It is expected that a total of 12 schools will participate. The allocation of the schools will be based on their current policy. Schools will be classified as an intervention school (IS) or as a control school (CS) based on their current use of the MASS intervention.

All YHC professionals of participating intervention schools will be offered a training in the MASS intervention at the start of the study.

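### MASS status is assigned by school, but the only clustering level named for the models is the school location; if a school has several locations, the false-positive rate may exceed 5%

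*Protocol article*

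**What the plan says.** Three cluster units appear in the protocol article, and nothing relates them to one another.

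- **Assignment: the school.** The Participants section states: "Schools will be classified as an intervention school (IS) or as a control school (CS) based on their current use of the MASS intervention". It also gives their number: "It is expected that a total of 12 schools will participate".
- **Power: the school class.** Power considerations has "Taking into account cluster randomization with Intra Class Correlation of 0.10" and, for cluster size, "assuming 15 participants per school class". Testing is described as "alpha 0.05 and a power of 0.80, in the case of one-sided testing".
- **Analysis: the school location.** Statistical analyses states: "As students are clustered within school locations multilevel analyses will be applied". No other level is named. Research condition enters the regression models as an independent variable, with baseline values of the outcome as covariates.

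The article does not say how many locations a school has, whether a location is a different thing from a participating school, or at which level the ICC of 0.10 applies.

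**The concern.** A comparison of schools with and without MASS has as many independent units per condition as there are schools. A random intercept for location alone judges the condition effect against variation between locations, as if each location had come to MASS or usual care on its own. Where several locations belong to one school, whatever that school's students share is counted more than once.

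The article itself makes shared school effects plausible. The criteria for a meeting with the student are set by each school (Table 1), as are the criteria for referral (Discussion). The absence data come from the school's own register (Data collection).

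At stake is the error rate of the effect analysis, which is a separate matter from the sample size. Ordinary differences in absence between schools could be reported as an effect of MASS. Schools are not randomised, so such differences are to be expected.

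**Working it through.** **1. The plan's own figure.** Inputs from Power considerations: 120 completers per arm, ICC 0.10, 15 per class, SD 30 h, one-sided alpha 0.05, power 0.80.

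- Design effect = 1 + (15 − 1) × 0.10 = 2.4
- Effective n per arm = 120 / 2.4 = 50
- Detectable difference = (1.645 + 0.842) × 30 × √(2/50) = 14.9 h

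This reproduces the stated 15 h, but only with one-sided testing; two-sided testing gives 16.8 h. The calculation takes the class as the cluster: 240 / 15 = 16 clusters, against 12 schools. The article gives no false-positive rate, so the rest is conditional arithmetic.

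**2. Set-up.** Assumptions: 12 schools split 6 v 6, 240 completers (20 per school), k equal locations per school with m = 20/k students each, and total variance 1. Write S for the school variance, L for the location variance (S + L = ICC) and R = 1 − ICC for the residual.

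Variance contributed by one school's mean:

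- True: S + (L + R/m)/k
- Assumed by a location-only model: (S + L + R/m)/k

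Let V be true divided by assumed. The actual one-sided rate at nominal 0.05 is then 1 − Φ(1.645/√V).

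**3. Two worked cases, ICC 0.10.**

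- *Two locations, all of the ICC at school level* (S = 0.10, L = 0, R/m = 0.09). True = 0.10 + 0.045 = 0.145. Assumed = 0.19/2 = 0.095. V = 1.53, rate 0.092.
- *Two locations, a quarter of the ICC at school level* (S = 0.025, L = 0.075). True = 0.025 + 0.165/2 = 0.1075. Assumed = 0.095. V = 1.13, rate 0.061.

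**4. Results, ICC 0.10, nominal 0.05** (one-sided / two-sided):

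| Locations per school | All ICC at school level | Half | A quarter | None |
|---|---|---|---|---|
| 1 | 0.050 / 0.050 | 0.050 / 0.050 | 0.050 / 0.050 | 0.050 / 0.050 |
| 2 | 0.092 / 0.113 | 0.072 / 0.081 | 0.061 / 0.065 | 0.050 / 0.050 |
| 3 | 0.113 / 0.150 | 0.084 / 0.101 | 0.068 / 0.075 | 0.050 / 0.050 |
| 4 | 0.127 / 0.173 | 0.092 / 0.114 | 0.072 / 0.082 | 0.050 / 0.050 |
| 5 | 0.135 / 0.189 | 0.098 / 0.123 | 0.075 / 0.087 | 0.050 / 0.050 |

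**5. Smaller ICC, all at school level** (one-sided). At ICC 0.05: 0.078 with two locations, 0.098 with four. At ICC 0.02: 0.064 and 0.073.

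**6. Simulation check** (40,000 null trials per setting, balanced, no baseline covariate). With all of the 0.10 at school level and a z test, the location-only model rejects 0.103, 0.136 and 0.142 one-sided for two, four and five locations; two-sided it rejects 0.136, 0.191 and 0.205. These are a little above the formula. With the school as the cluster, two locations per school and t on 12 − 2 = 10 degrees of freedom, the rate is 0.045 to 0.050 one-sided. With z in place of t it is 0.060 to 0.063, so the degrees of freedom matter as well as the level.

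**The case against.** The strongest reply is that the premise is never stated. The phrase about locations occurs once, and it may simply mean the 12 participating schools. If MASS use was classified site by site, the location is the assigned unit and the level is right. This stands: no error rate above 5% can be shown from the text alone.

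A second reply is that the list of random effects belongs in a fuller analysis plan, and that the Covariates section records the school attended. This stands in part. A fuller plan may add a school level, and the article does not exclude one. But the article is not silent here: it names a level, and that level is not the one named for assignment. Recording the school is not a remedy by itself either. Condition is constant within a school, so school as a fixed effect would be collinear with it.

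A reader might infer two stronger things, and the documents support neither.

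- *That the test rejects a true null two to four times too often.* That needs essentially all of the 0.10 at school level and two-sided testing (0.113 / 0.05 = 2.3 times with two locations), and about five locations with a z test to reach four (0.205 / 0.05 = 4.1). The only sidedness the article states is one-sided. There, two locations with a quarter of the ICC at school level give 0.061 / 0.05 = 1.2 times, and the simulated extreme gives 0.142 / 0.05 = 2.8 times.
- *That standard errors are too small in every two-group model.* That is untrue with one location per school or with no school-level variance. Adjustment for baseline may also shrink the ICC by an unknown amount, and the logistic models were not simulated.

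**Conclusion.** The mismatch is real: the unit named for clustering in the models is not the unit that carries the condition. Its consequence is conditional. If some schools contribute several locations and absence varies between schools, a location-only model understates the standard error of the MASS effect.

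Under the assumptions set out above, including ICC 0.10 with a quarter to all of it at school level and one-sided testing, the false-positive rate is about 0.06 to 0.14 in place of 0.05. With no school-level variance, or one location per school, the choice of level causes no inflation. The number of locations, the level of the ICC and the 6 v 6 split are assumptions of this check and are not given in the article. The point merits a correction of wording; it does not show that the planned test is invalid.

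**What to change.** In Statistical analyses, state that the multilevel models include a random intercept for the school, the unit classified as intervention or control, with location nested within it where a school has more than one. State that condition in the linear models is tested with small-sample degrees of freedom based on the number of schools (about 10 with 12 schools, for example by Kenward-Roger), and that the logistic models use a comparable small-cluster correction. Say in the same place how school, location and class relate.

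The cost is a sentence or two; the school attended is already recorded. Where schools have several locations, the confidence interval widens. As a guide, if the whole ICC of 0.10 sits at school level with 20 completers per school, the design effect is 1 + 19 × 0.10 = 2.9, the one-sided detectable difference is 16.4 h, and power at 15 h is 0.735. If school and location are the same unit, the clustering level does not change.

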## Discussion

Medical absenteeism is positively associated to early school dropout and may result in physical, mental, social and work-related problems later in life. The aim of the MASS intervention is to limit the medical absenteeism of students by arranging appropriate care, educational adjustments and adequate support [19, 21]. This paper describes the design of a controlled before-and-after study, which aims to evaluate the effectiveness of the MASS intervention as well as its contributing factors and interfering factors among intermediate vocational education school students.

It is hypothesized that implementation of the MASS intervention and incorporating a referral to a YHC professional is effective in terms of reducing medical absenteeism. Results of this study will show whether the YHC professional added value in the MASS intervention. Moreover, the study will provide insight in which factors contribute and/or moderate to the intervention’s effectiveness and may provide useful suggestions for improvement.

A strength of this study is that it will be conducted in the daily setting schools and YHC practice, which will facilitate future implementation. The participating schools and YHC professionals cover the urban and rural areas of the Netherlands, which will support the generalizability of our findings. Nevertheless, the schools and students are not randomized which can result in differences between the groups. We have tried to minimize this potential effect by correcting for potential confounders. Another strength is that we look at the extent to which the MASS intervention is applied by de YHC professional and gain insight into the care provided by the school to the individual students.

As the MASS intervention had already been implemented at the intervention schools, we could not capture strict criteria for referral to the YHC professional. The criteria for referral to a YHC professional were determined by each individual school which is in line with the MASS protocol, which may result in a variety of used criteria. On the other hand, this will give a realistic approach of the effects of the implementation of the MASS intervention. Also, the MASS-protocol requires great commitment of the schools to identify and refer students to YHC professionals [43]. It is therefore questionable how many students eventually will be identified and/or referred to the YHC professional.

In conclusion, the premise is that students with high rates of medical absenteeism receiving a customized reintegration plan and supervision from school and the YHC professional show a reduction in medical absence and easier return back to school compared to students receiving usual care. When MASS including the use of a YHC professional is effective, a comprehensive evaluation of full implementation of the MASS intervention at schools may follow.

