**Discussion:**

It is hypothesized that implementing the MASS intervention including a referral to a YHC professional on indication, will result in a lower level of medical absenteeism and a lower level of school drop outs among intermediate vocational education students compared to students receiving usual care. The study will provide insight in the effectiveness of the intervention as well as in factors moderating the intervention’s effectiveness.

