In 2012, the Medical Advice for Sick-reported Students (MASS) intervention was developed [19] to address medical absenteeism more actively within students attending pre-vocational secondary education, the school level preceding intermediate vocational education. The aim of the MASS intervention is to limit medical absenteeism by arranging appropriate care, educational adjustments and adequate support for students [21]. The intervention focuses on the factors associated with extensive medical absenteeism: somatic, mental and physical complains [9, 22–25], poor lifestyle [11] and psychological, family and social problems of sick-reported students [9]. The schools and the YHC professionals collaborate directly within the MASS intervention to design and monitor a management plan that aims to optimize students’ health and maximize students’ participation in school activities [19, 25] In an effect study Vanneste et al. found a reduction of 15.1% in medical absenteeism among pre-vocational secondary education school students after implementing the MASS intervention [19].

As students in pre-vocational secondary education schools often continue their education at intermediate vocational education schools, medical absenteeism might be associated with the same determinants in both groups of students. Despite potential similarities between intermediate vocational education and pre-vocational secondary education students, there are also clear differences that need to be taken into account in designing interventions. Students in intermediate vocational education schools, for instance, are generally aged between 15 and 25 years old. Furthermore, the level of medical absence is often larger at intermediate vocational education schools and its nature is often more complex due to underlying biopsychosocial factors and financial problems. As a result, the MASS intervention has been adapted for intermediate vocational education schools and is currently being applied at several schools in the Netherlands [26–28]. However, evidence for its effectiveness is thus far lacking.

The aim of this study is to evaluate the effectiveness of the MASS intervention at intermediate vocational education schools, with a focus on the efforts of the YHC professional, in terms of reducing students’ medical absenteeism and early dropping out of school. In addition, we will assess to what extent biopsychosocial and other factors may influence the effect of the intervention.

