## Methods/Design

### Study design

A controlled before-and-after study with a follow-up period of 6 months will be conducted. Students with extensive medical absence attending schools in which the MASS intervention has been implemented (intervention group) are compared to students attending schools in which the MASS intervention has not been implemented (control group).

The Medical Ethical Committee of Erasmus University Medical Centre Rotterdam has declared that the Medical Research Involving Human Subjects Act (also known by its Dutch abbreviation WMO) does not apply to this research protocol and issued a declaration of no objection (i.e. formal waver) for this study (MEC-2015-614). Therefore, the study can be carried out without further approval by an accredited research ethics committee.

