### Intervention

#### Intervention group: the MASS intervention

The MASS intervention designed for intermediate vocational education schools consists of five steps: an active approach by the school after the first sick report, a meeting between student and school, a YHC professional referral if needed, the actual YHC professional consultation, and the further monitoring of the medical absenteeism and reintegration of the student [31] (Table 1).

**Table 1 Tab1:** Description of the key steps of the MASS intervention

Step	Description
1	The school contacts the student actively in case of medical absence and asks about the context of the sickness report and condition of the student.
2	The school organizes a meeting with the student (and parents if student is <18 years old) in case of extensive medical absenteeism (criteria predefined by each individual school, apart from the MASS criteria).
3	The school refers the student to a YHC professional if considered to be needed.
4	A YHC consultation between student and YHC professional is organized
5	The school is responsible for monitoring the medical absenteeism and school-related implementation of the reintegration plan, if created.

*MASS* Medical Advice for Sick-reported Students

*YHC professional* Youth health care professional

The intervention focuses at two levels; the school level and the individual level. The implementation of the MASS intervention at school level includes agreements on how to actively monitor student absence, approach students with extensive medical absence by personal contact, request a consultation with the YHC professional, and arrange a follow-up for each student in the Care Advisory Team (CAT). The CAT includes social workers, attendance officer, YHC professionals, teachers and a Youth Care Office representative.

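### The Discussion promises to show whether the YHC professional added value, but the stated design identifies only the effect of the whole MASS package

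*Protocol article*

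**What the plan says.** - **Claim.** The Discussion states: "Results of this study will show whether the YHC professional added value in the MASS intervention". The sentence before it hypothesises that MASS with YHC referral reduces medical absenteeism. The aim at the end of the Background is to evaluate effectiveness "with a focus on the efforts of the YHC professional".
- **Comparison.** Under Study design, students with extensive absence at schools that have implemented MASS are compared with such students at schools that have not. Under Statistical analyses, "The research condition will be included as an independent variable".
- **Content of the package.** Table 1 lists five steps: contact by the school, a meeting with the school, referral, the YHC consultation, and monitoring by the school. On Step 3: "The school refers the student to a YHC professional if considered to be needed". The Discussion adds: "The criteria for referral to a YHC professional were determined by each individual school".
- **Controls.** Care as usual generally includes referral to a YHC professional when the student asks for it.
- **YHC-specific material.** Measurements lists adherence to the MASS protocol and the perceived value of MASS. Statistical analyses has experiences with the YHC elements evaluated descriptively. The moderators named there are student characteristics, and consultation is not among them.
- **Hypothesis.** The Abstract's version is at package level: "implementing the MASS intervention including a referral to a YHC professional on indication" is expected to lower absenteeism and dropout compared with usual care.

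**The concern.** The study has one between-group contrast, and the Discussion draws two messages from it: that MASS works, and that the YHC professional adds value within MASS. Only the first has a comparison behind it.

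The wording fixes in advance how results will be read. Lower absenteeism at MASS schools could come from the school's contact, meeting and monitoring, yet would be announced as evidence for the YHC professional. A null result could be read as the YHC professional adding nothing, although the Discussion itself doubts how many students will be identified or referred.

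**Working it through.** **1. The plan's own figure, and what it refers to.** Inputs from Power considerations: 120 completers per group, ICC 0.10, 15 per class, SD 30 h, one-sided alpha 0.05, power 0.80.

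- Design effect: 1 + (15 − 1) × 0.10 = 2.4
- Effective number per group: 120 / 2.4 = 50
- Detectable difference: (1.645 + 0.842) × 30 × √(2/50) = 14.92 h

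The stated 15 h is reproduced. It refers to intervention group against control group, that is, to the package.

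**2. Does any stated analysis isolate the consultation?**

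| Stated analysis | What it compares | Isolates the YHC consultation? |
|---|---|---|
| Effect model | MASS schools with usual-care schools | No: the five steps come as one package, and controls may also see a YHC professional |
| Moderation | Effect by student characteristics | No: consultation is not a listed moderator |
| YHC-specific outcomes | Adherence, perceived value | No: no effect on absenteeism is estimated |

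**3. Why one contrast is not enough.** Let D be the package difference, S the effect of everything in MASS other than the consultation, Y the consultation's effect among those consulted, and f the share consulted. Ignoring YHC use by controls,

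D = S + f × Y.

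The article does not give f, so the values below are assumed. D is set to 15 h for illustration.

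| f (assumed) | S if Y = 0 h | S if Y = 15 h |
|---|---|---|
| 0.10 | 15 h | 15 − 1.5 = 13.5 h |
| 0.25 | 15 h | 15 − 3.75 = 11.25 h |
| 0.50 | 15 h | 15 − 7.5 = 7.5 h |
| 1.00 | 15 h | 15 − 15 = 0 h |

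Every cell gives the same observed 15 h. Knowing f would not help, since S and Y would still be two unknowns in one equation. YHC use among controls adds a further unknown.

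**4. The contrast within MASS schools.** Consulted and non-consulted students at MASS schools could be compared, but referral depends on judged need and on school-specific criteria. The two sets therefore differ in need and in school before any consultation takes place. The article gives no basis for the direction or size of the resulting bias.

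Precision is a second limit. With 120 intervention completers, SD 30 h, one-sided 0.05 and 80% power, the detectable difference is 2.487 × 30 × √(1/n₁ + 1/n₀), ignoring clustering. The last column multiplies by √2.4, which carries the plan's design effect over unchanged. That is an assumption, since clustering may cost less in a comparison made inside schools.

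| f (assumed) | n₁ / n₀ | No clustering | Design effect 2.4 |
|---|---|---|---|
| 0.10 | 12 / 108 | 22.7 h | 35.2 h |
| 0.25 | 30 / 90 | 15.7 h | 24.4 h |
| 0.50 | 60 / 60 | 13.6 h | 21.1 h |

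**The case against.** The strongest reply is that this is one loosely worded sentence. The hypothesis, comparison, model and concluding paragraph all stay at package level, and no outcome, test or sample size depends on a component claim. That stands, and it confines the point to what the article says it will show.

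A second reply is that added value may mean the YHC-specific outcomes: adherence, perceived value, and students' appreciation of the consultation. This reading is possible. But the sentence follows a hypothesis about reducing absenteeism and does not mention perception, and the Measurements item concerns the perceived value of MASS as a whole. If this was the meaning, the sentence needs the same rewording.

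A third is that the Discussion already discloses the lack of randomisation, the varying referral criteria and the uncertain number referred. It does, but it does not say that the consultation's effect cannot be separated, and the claim stays unqualified.

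Three stronger readings are tempting, and the article does not support them:

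- *No analysis plan could ever address the component.* A reader might infer this, but Data collection provides for exposure and adherence items and school records of support given. A fuller plan could specify an adjusted exposure analysis. With referral by indication, it would be exploratory.
- *No student receives the school's steps without a consultation.* No study condition is defined that way, but referral is selective, so unreferred students at MASS schools may receive exactly that care.
- *The steps divide cleanly into school and YHC parts.* Referral in Step 3 is an act of the school, and Step 5 partly carries out a reintegration plan formulated in the consultation. This overlap makes attribution harder still.

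**Conclusion.** The point holds as a correction to a stated conclusion. As written, the sentence claims a component effect that the stated design cannot identify. There is one package contrast, controls have some YHC access, and consultation within MASS schools is selected by need and by school.

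No size in hours is claimed. The hour figures above are illustrations with an assumed share consulted and, in the decomposition, no YHC use among controls. The conclusion itself rests only on the stated comparison and referral rule.

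A reader might go on to infer that the package comparison or the 15 h power figure is undermined. Neither follows from this point: the comparison matches the Abstract's hypothesis, and 15 h is reproduced for that contrast. The next step named in the concluding paragraph, an evaluation of full implementation, needs only the package result.

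**What to change.** 1. Replace the Discussion sentence with one of package scope: the results will show whether "implementing the MASS intervention including a referral to a YHC professional on indication" reduces medical absenteeism compared with usual care.
2. In the Background aim, tie the focus on the YHC professional to the process outcomes under Measurements: adherence to the MASS protocol and perceived value.
3. Label any contrast of consulted with non-consulted students as exploratory, adjusted or not, and give referral by need and school-set criteria as the reason.

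Reporting the share of students consulted in each group would help readers interpret the package result, but it is optional.

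The cost is a few reworded sentences, with the primary analysis and sample size unchanged. The downside is that the study gives up the component claim. Keeping it as a confirmatory claim would need a condition with the school's steps but no YHC referral, and classifying schools only by whether they currently use MASS does not provide one.
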